#### Neuroimaging analyses

Treatment-related differences in both structural and functional MRI datasets will be assessed using mass-univariate voxelwise General Linear Models. Thus, repeated measures ANOVA functions available in SPSS will be computed to examine between- and within-group effects of treatments. A standard threshold of *p* < 0.05 will be applied for ROI data, correcting for multiple comparisons.

### Ethical issues

Written informed consent will be obtained from all participants before randomisation. Participants will be provided with a general overview of the aims and characteristics of the study and the interventions before signing the informed consent. They will also be assured that they will be participating voluntarily and can withdraw at any time from the study with the guarantee that they will continue to receive the most appropriate medical treatment prescribed by their general practitioner. The study will be performed in accordance with the ethical standards laid down in the 1964 Declaration of Helsinki and its subsequent updates. The FSJD Research Committee Board evaluated and approved the study protocol in May 2015 (PIC-102-15). All patient data will be treated as confidential and only the research team will be allowed to access it after recodification of name and personal identity number (so no individual can be directly identified). Only the principal investigator of the study will have access to the code key which will be stored separately in a safe place in accordance with Spanish legislation. All data will be computer processed and stored. Blood samples will be stored, encrypted, and will not be directly traceable back to individuals. Blood samples will be used only in ways to which the participants consented and may only be made available to a new research project after Ethical Research Committee approval and participants provide a new agreement. Furthermore, the participants have the right to request, without explanation, that their samples be destroyed or made completely anonymous.

### Forecast execution dates

Initial recruitment of patients: January 2016

Finalisation of patient recruitment: January 2017

Finalisation of patient monitoring period: April 2018

Publication of results: December 2018

## Discussion

The study described here will evaluate, for the first time, the cost-utility of MBSR for FMS patients compared with usual care and with an empirically-validated intervention (FibroQol) which proved to be cost-effective in such patients in a high-quality RCT [41]. Therefore, this is a 3-armed RCT in which we include an active control condition (psycho-education) that permits us to control the “frustrebo response” (disappointment among control participants at not receiving treatment) associated with waiting-list and TAU conditions [92]. The RCT was designed following the CONSORT recommendations, the economic evaluation was planned following the updated ISPOR core recommendations for cost-effectiveness analyses alongside RCTs, the sample size in each study arm is sufficiently large and the follow-up period is sufficiently long to capture important costs and outcomes. If our trial results are sufficiently robust, MBSR programmes might be delivered as part of a strategic, coherent or appropriately resourced approach for patients with FMS in the healthcare context [80, 93]. According to Gotlink et al. [80], “*further research should also look more into the mechanisms whereby these therapies (MBSR-MBCT) are efficacious*”. In the present RCT, we are not only interested in the clinical effects of MBSR at long-term, but also in the “process” psychological variables and neurobiological changes that contribute to them, which is a current source of interest and debate in the scientific literature [89, 94].

One of the main risks in this study may be dropouts. A sensitivity analysis using a per protocol strategy will be performed to determine the impact of the adherence to the protocol in both the MBSR and FibroQoL groups. This RCT is intended to be as naturalistic as possible, so prescribed drugs are permitted throughout the study. The effects of these drugs on clinical and biological outcomes may constitute another study limitation. However, no baseline differences among study arms regarding medical drugs are expected (due to randomisation) and sub-analyses evaluating the potential effects of the main pharmacological treatments (e.g., antidepressants) on the outcomes will be performed. Moreover, received pharmacological treatment may not be stable over time (e.g., initiating antidepressant treatment due to a depressive episode, changing principle/dose of other drugs due to variations in clinical symptoms, or starting individual therapy with a psychologist) so it is probable that some patients will be excluded from the study due to drastic changes in their treatment. Patients will be asked at post- and follow-up assessments for details about changes in medical treatment received and the clinicians will check the pharmacological treatment history in the patients’ clinical chart.

To our knowledge, this study represents the first attempt to detect structural and functional brain changes and inflammatory marker variations after MBSR in patients with FMS. Indeed, few studies have focused on exploration of the neural and inflammatory underpinnings of psychological treatments in chronic pain patients. We hope that our work will offer new advances in understanding the psychophysiological processes altered by mindfulness and their relationship with clinical outcomes. Understanding of how mindfulness changes these variables will in turn increase our understanding of the role of the brain and the immune system in FMS. Furthermore, determining FMS profiles according to psychological and brain/immune variables may also allow prediction of treatment response in patients with this diagnosis. Given that patients with FMS usually present comorbidities with psychiatric disorders (such as depression or anxiety) and other central sensitivity syndromes (such as chronic fatigue syndrome), the results from this study may have translational value.

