Usual contraindications for scanning at 3Tesla and for measuring cytokine levels have been taken into account to establish the following additional inclusion/exclusion criteria for the biomarkers sub-study:*Inclusion criteria*: 1. Female gender. 2. Right-handed.*Exclusion criteria*: 1. Infection/cold symptoms on the day of blood extraction. 2. Needle phobia. 3. BMI > 36 kg/m^2^ or weight > 110Kg. 4. Neoplastic illnesses, infection, cardiopulmonary, vascular, or other internal conditions (collected from the medical history). 5. Use of oral or local corticosteroids or anticytokine therapy. 6. Consuming more than 7 caffeine units per day (1 caffeine drink will be permitted on the day of the study. 8. Smoking more than 5 cigarettes per day (no smoking will be permitted on the scanning visit days prior to scanning or whilst in the centre). 9. Cannot be evaluated by means of magnetic resonance imaging (MRI) (due to claustrophobia, metal implants, pace-makers, etc.). 10. Acute pain not -related to FMS on the day of the study (e.g. headache, lumbar pain). 11. Being pregnant or breastfeeding. It is important to point out that patients presenting neuroradiological alterations during MRI at baseline will be excluded from the sub-study. Patients will be allowed to continue with their stable medical treatment although, to reduce the effects of medications on biomarkers, they will be required to refrain from taking occasional (rescue) analgesic drugs (e.g., non-steroidal anti-inflammatory drugs, paracetamol) 72 h prior to the MRI and blood extraction. Changes in pharmacological/non-pharmacological treatment will be monitored throughout the study and may be a cause of drop-out from the final analyses.

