#### Primary outcome measure

The *Revised Fibromyalgia Impact Questionnaire* (FIQR) [56, 57] includes 21 individual items that are all answered on an 11-point numeric rating scale from 0 to 10, with 10 reflecting greater impairment. The time frame is the previous 7 days and the items are distributed into three associated domains: “physical function” (9 items); “overall impact” (2 items that address the overall impact of FM on functioning and symptom severity); and “severity of symptoms” (10 items; pain, energy, stiffness, quality of sleep, depression, memory problems, anxiety, tenderness to touch, balance problems, and sensitivity to loud noises, bright lights, odours, and cold temperatures). The scoring system is straightforward: the physical function domain (0 to 90) is divided by 3, the overall impact domain (0 to 20) is not transformed, and the severity of symptoms domain (0 to 100) is divided by 2. The FIQR total score (0 to 100) is obtained by adding the three domain scores. The FIQR has been shown to be a psychometrically sound instrument, is clinically useful as it can be completed by patients in less than 2 min and scored in approximately 1 min, is recommended as a primary efficacy endpoint measure in FMS clinical trials, and is the “gold standard” assessment measure for multidimensional functional status in FMS patients [58].

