#### Analysis of clinical efficacy

To assess treatment effects, we will perform Intention-to-Treat analyses, which will include all participants who undergo random allocation, using multiple imputation to replace missing values.

To study the differences in the primary outcome and in each of the secondary outcomes between groups, linear mixed-effects models [85] will be prepared using Restricted Maximum Likelihood to estimate the parameters. Comparisons amongst treatment groups at post-treatment and at 12-month follow-up will be computed with estimates derived from the linear mixed-effect models (use of the Bonferroni method to adjust the significance level of the pairwise contrasts). Calculations of between-groups effect sizes using Cohen’s *d* with its 95 % confidence interval will be based on the pooled standard deviation at baseline. Finally, to make the findings from the present RCT meaningful to clinicians, the number-needed-to-treat (NNT) [86] in the MBSR condition will be reported. Taking the Luciano et al. [87] NNT approach as our reference, we dichotomise participants into responders or non-responders using three separate cut-off criteria: (a) ≥ 20 % reduction on the FIQR total score from baseline to post-treatment; (b) ≥ 50 % reduction on the FIQR total score from baseline to post-treatment; and (c) number of patients crossing a cut-off point (reaching no worse than mild functional impairment; FIQR total score < 39).

Given that some pharmacological treatments may interfere with cytokine levels [88], differences in cytokine levels between patients taking vs. not taking antidepressants will be evaluated.

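### The protocol promises an analysis of everyone randomised, yet expects some patients to be excluded from the study for treatment changes after randomisation

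*Protocol article*

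**What the plan says.** Three places in the protocol article bear on who is analysed.

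- **Analysis of clinical efficacy:** the plan is for "Intention-to-Treat analyses, which will include all participants who undergo random allocation, using multiple imputation to replace missing values". Linear mixed-effects models then compare the arms at post-treatment and at 12 months.
- **Discussion, paragraph on limitations:** treatment may not stay stable. The examples given are "initiating antidepressant treatment due to a depressive episode, changing principle/dose of other drugs due to variations in clinical symptoms", and starting individual therapy with a psychologist. The sentence concludes that "it is probable that some patients will be excluded from the study due to drastic changes in their treatment". The same paragraph says: "This RCT is intended to be as naturalistic as possible, so prescribed drugs are permitted throughout the study".
- **Eligibility criteria and Multi-stage recruitment process, end of the paragraph on the biomarker sub-study:** "Changes in pharmacological/non-pharmacological treatment will be monitored throughout the study and may be a cause of drop-out from the final analyses".

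A per-protocol analysis is described separately. The Discussion ties it to adherence in the MBSR and FibroQoL arms, and the cost-utility section gives attendance at 6 or more sessions as the criterion. Neither description mentions changes in other treatment.

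**The concern.** A set that contains every randomised patient cannot also lose patients for something that happened after randomisation. As worded, the efficacy section and the Discussion give two different populations for the main comparison.

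The exclusion is unlikely to be harmless, because the document links treatment change to symptoms. A depressive episode and symptom variation are given as reasons for change. The FIQR symptom domain covers "pain, energy, stiffness, quality of sleep, depression, memory problems, anxiety, tenderness to touch", and the HADS measures anxiety and depression as a secondary outcome. Patients removed for such changes would therefore tend to be selected on the outcome, and the arms could lose different numbers.

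There is also a tension with the comparator. The section on the TAU control group describes usual care as mainly pharmacological and adjusted to each patient's symptoms, and all three arms receive it. Adjusting drugs to symptoms is thus part of what is being compared. If the exclusion reached the cost-utility analysis, it would also remove patients whose medication and service use had changed markedly. That consequence is inferred; the cost-utility section does not state it.

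**Working it through.** **Step 1: the passages side by side.**

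| Place | Who is in the analysis | Scope |
|---|---|---|
| Analysis of clinical efficacy | all randomised, missing values imputed | primary and secondary outcomes |
| Discussion | some probably excluded for drastic treatment change | the study; the preceding sentences name clinical and biological outcomes |
| Eligibility section | treatment change may remove a patient from final analyses | closes the biomarker paragraph |
| Per-protocol analysis | session attendance | sensitivity analysis |

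The first two rows conflict. The third need not conflict with the first if it is read as a sub-study rule. The fourth does not cover treatment change, so it does not resolve the conflict.

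**Step 2: how much exclusion could matter.** The plan has no figure of its own to reproduce here. Only the 0.53 SD from the sample-size section is borrowed, as a scale. Everything else in this step is assumed.

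Let y be the outcome in SD units, higher meaning worse, with TAU ~ N(0, 1) and MBSR ~ N(-0.53, 1). The probability of exclusion is 1/(1 + exp(-(a + b·y))), the same rule in both arms. Patients still in the analysis are compared as complete cases. For each arm the retained mean is ∫ y·(1 - p(y))·φ(y - μ) dy ÷ ∫ (1 - p(y))·φ(y - μ) dy, evaluated numerically. Differences are in the unselected SD, close to the plan's use of the baseline SD for Cohen's d.

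| Rule | Excluded TAU / MBSR | Retained means TAU / MBSR | Difference |
|---|---|---|---|
| Worse likelier out, a = -3, b = 1.5 | 9.7% / 5.2% | -0.118 / -0.597 | 0.479 |
| Worse likelier out, a = -2.5, b = 2 | 17.3% / 9.1% | -0.230 / -0.662 | 0.431 |
| Improved likelier out, a = -3, b = -1.5 | 9.7% / 16.7% | 0.118 / -0.337 | 0.455 |
| Improved likelier out, a = -2.5, b = -2 | 17.3% / 29.3% | 0.230 / -0.163 | 0.394 |

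In the first two rows the shortfall is (0.53 - 0.479)/0.53 = 10% and (0.53 - 0.431)/0.53 = 19%. With 60 per arm they correspond to about 6 to 10 TAU patients (60 × 0.097 and 60 × 0.173) and 3 to 5 MBSR patients (60 × 0.052 and 60 × 0.091).

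**Step 3: a second illustration, with no true effect.** If a fraction p of an arm is excluded and exclusion correlates ρ with a worse outcome, the retained mean shifts by -ρ·φ(z)/(1 - p), where z is the upper-p normal quantile. For ρ = 0.5, with 20% lost from control and 5% from MBSR, the shifts are -0.175 and -0.054, so the arms differ by 0.121 SD against MBSR. For ρ = 0.3, with 20% and 10% lost, they are -0.105 and -0.058, a difference of 0.046 SD. Over ρ of 0.3 to 0.5 and losses of 15% v 5%, 20% v 10% and 20% v 5%, the spurious difference is about 0.05 to 0.12 SD. Equal losses with equal selection give zero.

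**Step 4: selection that differs by arm.** Suppose TAU exclusions are unrelated to outcome (retained mean 0) while MBSR loses its worse patients under the first rule (retained mean -0.597). The difference is then 0.60, above the true 0.53. The direction therefore depends on a selection pattern that the documents do not describe.

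**The case against.** **It is a remark about limitations.** The Discussion sentence predicts what is probable; the efficacy and cost-utility sections contain no exclusion for treatment change. That is fair, and it limits how firmly one can say patients will be dropped. It does not remove the conflict, because the sentence announces exclusion from the study as expected conduct.

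**Excluded patients may simply be withdrawn and imputed.** The paragraph opens with dropouts, so this reading is open, and the illustrations above do not model the planned multiple imputation or mixed models. The text does not confirm the reading, however. Discarding outcomes after a symptom-driven change and imputing them largely from patients who did not change treatment could still bias the result.

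**The eligibility sentence concerns only the biomarker sub-study.** This largely stands. The sentence follows rules on stable medication and rescue analgesics meant to protect the biomarker measurements. A reader might take it as a second general exclusion rule; its position does not support that.

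**Assessors are blind.** The Procedure section has the face-to-face interviews done by psychologists blind to allocation. A reader might infer that exclusions would be decided with the arm known. The documents do not show that. They do not say who decides, and they are silent on whether the clinicians who check the charts are blind.

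**Definitions belong in the analysis plan.** Leaving *drastic* undefined in an article is no fault in itself. The point is that the article states two rules that do not fit together.

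**Conclusion.** The conflict between the efficacy section and the Discussion is real and rests on the wording alone. The eligibility sentence adds to the uncertainty but most naturally belongs to the sub-study. Whether the main comparison would be harmed depends on which rule is followed.

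If patients were dropped, the size of the bias cannot be known from the documents. Under the assumed common rule with worse patients likelier to leave, and a complete-case analysis, 0.53 SD becomes about 0.48 to 0.43, an understatement of roughly 10% to 19%.

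A reader might infer that the bias turns in favour of MBSR if improved patients who cut their drugs are the ones excluded. The calculation does not support that: under a common rule this also attenuates the difference, to about 0.46 and 0.39, because more MBSR patients leave. Overstatement needs selection that differs between arms, and the documents say nothing on which to judge it. Nor do they show that the cost-utility analysis will exclude these patients; its only stated exclusion is a sensitivity analysis on attendance.

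**What to change.** Reconcile the efficacy section, the Discussion and the eligibility section with a statement to this effect:

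- A change in treatment after randomisation is not a reason to remove any randomised patient from the effectiveness or cost-utility analyses.
- FIQR, EQ-5D-5L, CSRI and the other scheduled outcomes continue to be collected after such a change.
- Exclusion for treatment change is used only in a labelled sensitivity analysis, with its rule fixed before data are seen.
- For the biomarker sub-study, results are reported with and without these patients, and the eligibility sentence is marked as applying to that sub-study.

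This concerns the analysis population and data collection only; it changes no patient's care. The cost is protocol wording, since details of treatment change are already to be collected at the post-treatment and follow-up assessments. The downside is some added noise from drug changes in the biomarker estimates that include everyone.
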